#### Assessment of the educational dimension of the PEP

Patient’s acquisition of knowledge and skills about his/her pain and treatment will be assessed using a questionnaire developed by our working group and administered at the beginning and at the end of the PEP. Scales evaluating the patient’s self-efficacy to participate actively in pain management and to communicate optimally with caregivers will be also used [28]. The patient’s feeling of changes in his health and its repercussion following the PEP will be retrospectively assessed using sensitive scales [29] particularly adapted to pain.

#### Assessment of participants’ satisfaction and educators’ satisfaction with the PEP

Standards tools recommended by the HAS will be adapted to cancer pain on the basis of those proposed by PLANETH Patient (Plateforme Normande d'Education Thérapeutique du Patient), a regional body whose particular mission is to harmonise TPE practices and their evaluation [30]. The questionnaires deal with the modalities of the workshops (duration, frequency), the benefits of pain management, the quality of the educators and their ability to efficient communication.

The assessment of the program and its benefits for patients will be also conducted with the caregiver-educators. It will evaluate the PEP impact on the educational team in terms of functioning, changes in practices and incorporation with the offer of local care, including communication with the attending physician.

#### Assessments addressed to the patients’ relatives

Patients’ relatives willing to participate to the PEP will have their own QoL evaluated by a self-questionnaire specifically developed in oncology and validated in French (CarGoQoL, [31]). Analgesic treatment adherence, assessment of knowledge and skills about patients’ pain and treatment, and satisfaction with the PEP will be evaluated in relatives using similar questionnaires which have been adapted to them.

#### Primary and secondary endpoints

The main judgement criterion in this study is the impact of pain on daily activities measured with the BPI. A score will be established by averaging the response on the 7 items of the subscale 9. The benefit of TPE on the impact of pain will be defined as a 2-point-decrease (on a scale of 10) between the values measured before and at the end of the PEP (at 8 weeks after inclusion). A 2-point decrease on the BPI scale correspond to a clinically significant improvement [32].

The first secondary endpoint is the proportion of patients adhering to the whole PEP (3 sessions), adherence being defined as the achievement of these 3 sessions for patients who undertook to follow them.

Other secondary endpoints are based on:

- Pain intensity and relief (BPI), its impact on QoL (subscale 9 of BPI, HADS), qualitative characteristics of pain (QDSA) and pain adherence.

- Patient’s knowledge and skills about pain, patient’s self-efficacy to actively manage pain, patient-reported impression of improvement.

- Participants’ satisfaction and educators’ satisfaction with PEP.

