### Study flowchart

For all the participants with signed consent form, assessments will be conducted at baseline and 8 weeks after inclusion (Fig. 2). For patients of the experimental PEP group, complementary assessments will be performed twice during the program.

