### Statistical analysis

#### Sample size calculation

The calculation of the number of subjects needed for statistical significance is based on the main judgement criterion and on the first secondary endpoint.

To meet the first primary objective (Step 5 of the study) building on a stepped-wedge design, the calculation of needed number of patients is based on a ≥ 2-point decrease of the mean score of the BPI subscale 9 at 8 weeks after inclusion, in the experimental PEP group compared to the control group (corresponding to a clinically significant improvement). The calculation takes into account that randomisation is done by clusters (patients belonging to a same cluster are not independent). Based on bilateral test and common-factor variances (2.5-point standard deviation in both groups (intraclass correlation coefficient = 0.05; 3 clusters per randomisation arm; alpha = 5%; power = 80%) it is estimated that 45 patients per arm equitably distributed between the 6 clusters, for a total of 90 assessable patients (Fig. 3).

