#### Data analysis

At every stage of the analysis, exploratory data will provide, for quantitative variables, mean, its standard deviation, median, quartiles, and missing data; for qualitative variables, frequencies and 95% confidence interval. Statistical tests and confidence intervals will be calculated with an overall error significance level of 5%. For the main objective (Step 5), statistical analysis will be done on the per-protocol population: it will concern assessable patients who have completed the whole program (3 sessions after the educational diagnosis).

Pain interference with daily life scores at 8 weeks post inclusion will be first compared between experimental PEP group and control group, in consideration of the correlation of data (generalized linear mixed model).

For the first secondary objective (Step 4), patients’ adherence to the PEP at the regional scale will be assessed using one-sided test comparing a proportion to a reference value.

For all the steps, a global analysis will be performed, taking into account the different periods of the study, clusters, and the care provided for each period, using a generalized linear mixed model for scales scores and for qualitative results obtained from questionnaires. This analysis will be adjusted to the patients’ demographic and clinical characteristics.

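### The benefit is worded as a before-to-after fall while the main comparison uses 8-week scores between groups, and baseline BPI interference is not named as a covariate

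*Protocol article*

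**What the plan says.** Three sections of the protocol article describe the main criterion.

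- **Primary and secondary endpoints.** The measure is BPI interference: "A score will be established by averaging the response on the 7 items of the subscale 9". The benefit "will be defined as a 2-point-decrease (on a scale of 10) between the values measured before and at the end of the PEP", with the end placed at 8 weeks after inclusion. The next sentence justifies 2 points as clinically significant.
- **Sample size calculation.** The target is a 2-point decrease in the "mean score of the BPI subscale 9 at 8 weeks after inclusion, in the experimental PEP group compared to the control group", with a "2.5-point standard deviation in both groups" and "intraclass correlation coefficient = 0.05". The result is 45 assessable patients per arm.
- **Data analysis.** "Pain interference with daily life scores at 8 weeks post inclusion will be first compared between experimental PEP group and control group", using a mixed model that allows for correlated data. No baseline term is named. A later global mixed model takes in period, cluster and care received, and adjusts for patients' demographic and clinical variables without listing them.

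On timing, the Study flowchart section states that for all consenting participants "assessments will be conducted at baseline and 8 weeks after inclusion".

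**The concern.** A before-to-after change and an 8-week group difference are different quantities. They have different standard deviations, and they respond differently to baseline differences between conditions. Read literally, the endpoint sentence cannot be applied to control patients, who attend no PEP.

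The silence on baseline matters more here than in a trial that randomises patients:

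- Randomisation is by cluster, and there are six.
- The Basse-Normandie cluster contributes PEP patients only.
- In the other centres, condition follows staff training, so staff know it when they enrol a patient.
- The main analysis is per protocol and keeps PEP patients who completed all three sessions. Control patients face no matching requirement.

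Each of these can leave the two conditions with different average interference at inclusion. A comparison of 8-week scores without baseline carries part of that difference into the estimated effect, and gives up precision that the baseline score could supply.

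**Working it through.** **1. Reproducing the stated sample size.** Inputs from the Sample size calculation section: difference 2, SD 2.5, two-sided 5%, power 80%, ICC 0.05, 3 clusters per arm.

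- Individual level, normal formula: 2 × [2.5 × (1.96 + 0.84) / 2]² = 24.5, so 25 per arm. The t-test version gives 26.
- Design effect at 15 per cluster: 1 + 14 × 0.05 = 1.70.
- 26 × 1.70 = 44.2, rounded up to 45 per arm. This matches the article.
- Normal-approximation power at 45 per arm: standard error = 2.5 × √(2 × 1.70 / 45) = 0.687; 2 / 0.687 − 1.96 = 0.95; power about 83%.

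No baseline-to-follow-up correlation enters. The same number results whether 2.5 is the SD of the 8-week score or of the change, so the arithmetic does not reveal which was meant.

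**2. What the choice of quantity does.** Assumptions: 2.5 is the SD of the 8-week score, baseline has the same SD, and the design effect stays at 1.70. The correlation r between baseline and 8 weeks is not in the article, so r = 0.3, 0.5 and 0.7 are tried.

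- Baseline-adjusted residual SD = 2.5 × √(1 − r²)
- Unadjusted change-score SD = 2.5 × √(2(1 − r))

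| r | Adjusted SD | Needed per arm | Power at 45 | Change SD | Needed per arm | Power at 45 |
|---|---|---|---|---|---|---|
| 0.3 | 2.38 | 40 | 86% | 2.96 | 60 | 69% |
| 0.5 | 2.17 | 33 | 92% | 2.50 | 43 | 83% |
| 0.7 | 1.79 | 23 | 98% | 1.94 | 26 | 96% |

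The needed numbers use the normal formula, for which the unadjusted 8-week score needs 25 × 1.70 = 42.5, so 43 per arm. Adjustment never needs more than that. An unadjusted change score needs more when r is below 0.5.

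**3. Patient-level precision.** The ratio of standard errors, adjusted to unadjusted, is √(1 − r²) = 0.954, 0.866 and 0.714. The reductions are about 5%, 13% and 29%.

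**4. Illustration of imbalance.** With equal SDs, a baseline difference d moves the unadjusted 8-week difference by r × d. For an assumed d = 0.5 and r = 0.5 this is 0.25 points, one eighth of the 2-point target. The article gives no value for d.

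**5. Is baseline BPI available?** The flowchart section has all participants assessed at baseline. The section on pain assessment lists the HADS and the QDSA as PEP-group measures and does not put the BPI among them. Against this, a footnote to Table 2 mentions control questionnaires only at 8 weeks, and the table itself is not shown. Baseline BPI in controls is therefore probable but not confirmed.

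**The case against.** The strongest reply is that the plan is more coherent than the endpoint sentence suggests. The sample size and data analysis sections agree on a between-group comparison at 8 weeks, and the endpoint section names the same score. Its 2-point sentence can be read as a clinical-relevance threshold, since the text that follows justifies it in that way. This stands: there are two versions of the quantity, not three competing ones.

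A reader might also infer that the trial could claim success from a fall within the PEP group, and that regression to the mean in patients selected for uncontrolled pain would then pass for a programme effect. The article does not support that. Every statement of the main comparison sets PEP against conventional care, and a fall common to both conditions cancels in that contrast.

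The reply continues that the global model may already include baseline BPI among its clinical variables, and that covariate lists are commonly left to the analysis plan. This stands in part. Baseline BPI is not excluded, but the adjustment is attached to the later global analysis and not to the first comparison. The endpoint wording is for the protocol to settle.

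Finally, the correlations and the 0.5-point imbalance are assumptions, and the percentages are at patient level. This stands in full.

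**Conclusion.** The wording mismatch is in the text: a within-patient fall in the endpoint section, an 8-week between-group difference in the sample size and analysis sections. No section names baseline BPI interference in the main comparison. Naming it is an essentially free improvement in precision and in protection against imbalance; it does not repair a demonstrated error.

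The size is modest and conditional. The patient-level standard error falls by about 5% to 29% for assumed r of 0.3 to 0.7. The gain in the treatment-effect standard error was not computed, since it depends on the cluster and period terms. Adjustment would also not remove all bias from analysing only PEP completers.

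Two stronger readings should be avoided. One is that 45 per arm is too small: the figure reproduces, and under the stated assumptions baseline adjustment raises power. Only an unadjusted change score with r below 0.5 would lower it, and the analysis section does not plan one. The other is that the trial was definitely powered on the raw 8-week score. The wording leans that way, but the article never says which quantity has the SD of 2.5.

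**What to change.** - State the primary endpoint once, as the between-condition difference in BPI interference score at 8 weeks.
- Name baseline BPI interference as a covariate in the primary mixed model, together with period and cluster.
- Relabel the 2-point fall as a clinical-relevance threshold, or report the share of patients reaching it as a secondary responder endpoint in both conditions, timed from inclusion so that it applies to controls.
- Say whether the SD of 2.5 is that of the 8-week score or of the change.
- Confirm in Table 2 that control patients complete the BPI at inclusion.

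If Table 2 confirms this, the cost is wording only, with no new data and no more patients. If it does not, the BPI must be added at inclusion for controls.

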### Statistical analysis

#### Sample size calculation

The calculation of the number of subjects needed for statistical significance is based on the main judgement criterion and on the first secondary endpoint.

To meet the first primary objective (Step 5 of the study) building on a stepped-wedge design, the calculation of needed number of patients is based on a ≥ 2-point decrease of the mean score of the BPI subscale 9 at 8 weeks after inclusion, in the experimental PEP group compared to the control group (corresponding to a clinically significant improvement). The calculation takes into account that randomisation is done by clusters (patients belonging to a same cluster are not independent). Based on bilateral test and common-factor variances (2.5-point standard deviation in both groups (intraclass correlation coefficient = 0.05; 3 clusters per randomisation arm; alpha = 5%; power = 80%) it is estimated that 45 patients per arm equitably distributed between the 6 clusters, for a total of 90 assessable patients (Fig. 3).

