**Fig. 3 Fig3:**
[figure not shown]
Expected distribution of patients according to the stepped-wedge design

Moreover, all 5 participating regions outside Basse-Normandie candidates for training their caregivers to TPE, will each include 15 assessable patients in the control group (before being trained). It will be therefore possible to compare, at the region scale, the effect of TPE implementation on daily activities.

To meet to the objective of the Step 4, the judgement criterion is the proportion of patients recruited in Basse-Normandie area adhering to the whole PEP.

Under the assumptions of p_0_ = 0.70, p_1_ = 0.85, α = 5%, and β = 10%, 80 patients are necessary (unilateral exact binomial test that compares a proportion to a reference value) in order to best characterize adhesion to the PEP in the region (Fig. 3).

Of these patients, 15 will be randomly assigned for participation of Basse-Normandie in the primary objective (Step 5 of the study).

Overall, 230 evaluable patients are required; it is therefore planned to recruit 260 patients in order to anticipate some non-assessable patients.

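### The 45 per arm and 80% power come from a parallel 3-versus-3 cluster calculation, not the planned stepped wedge, and do not match the 75 controls counted later

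*Protocol article*

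**What the plan says.** All references are to the protocol article.

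- **Sample size calculation, primary objective.** The section says that it rests on the stepped-wedge design. The target is a "2-point decrease of the mean score of the BPI subscale 9 at 8 weeks after inclusion", program versus control, with a "2.5-point standard deviation in both groups". The remaining inputs are "intraclass correlation coefficient = 0.05; 3 clusters per randomisation arm; alpha = 5%; power = 80"%, two-sided. The result is that "it is estimated that 45 patients per arm equitably distributed between the 6 clusters, for a total of 90 assessable patients".
- **Sample size calculation, text after Fig. 3.** It adds that "all 5 participating regions outside Basse-Normandie candidates for training their caregivers to TPE, will each include 15 assessable patients in the control group". Basse-Normandie needs 80 patients for the adherence objective (Step 4), and 15 of these are drawn at random for the primary objective. The total follows: "Overall, 230 evaluable patients are required".
- **Study design.** All enrolled Basse-Normandie patients receive the educational approach. The five national centres enter gradually and are compared before and after training.
- **Data analysis.** The global analysis is a mixed model with period, cluster and the care given in each period.

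**The concern.** The only design inputs to the calculation are the intraclass correlation and "3 clusters per randomisation arm". That describes two sets of three clusters, each under one condition for the whole trial. In a stepped wedge, most of the information comes from comparing a cluster with itself before and after its switch, and some of it is lost in separating the program effect from calendar time. A parallel formula contains neither feature, so its power is not a property of this trial.

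The counts also disagree: 45 controls in one paragraph and 75 in the next. A reader cannot tell whether the primary comparison holds 90 or 165 patients, how they divide between conditions, or what power the trial has for its main objective.

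**Working it through.** **1. Reproducing the plan's figure.** Inputs from the sample size section: difference 2, SD 2.5, two-sided alpha 5%, power 80%, ICC 0.05, 3 clusters per arm. With 90 patients over 6 clusters, cluster size is m = 15.

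- Per arm without clustering, normal formula: 2 × (1.96 + 0.84)² × 2.5² / 2² = 24.5, so 25. The t-test version gives 26.
- Design effect: 1 + (15 − 1) × 0.05 = 1.70.
- 26 × 1.70 = 44.2, which becomes 45 = 3 × 15. The normal version gives 25 × 1.70 = 42.5, so 43.
- At 45 per arm: SE = √(2 × 6.25 × 1.70 / 45) = 0.687; 2 / 0.687 = 2.91; normal-test power = Φ(2.91 − 1.96) = 82.9%.

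The parallel formula returns the stated 45. It has no period term and no within-cluster crossover.

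**2. Arms against design.** Basse-Normandie has no control patients, and each of the five national centres has patients under both conditions. No three clusters form a control arm, and 45 controls cannot be shared among six clusters when one has none.

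**3. Counts.** Controls: 5 × 15 = 75. Basse-Normandie: 80, of which 15 enter the primary objective and 65 do not. That leaves 230 − 80 − 75 = 75 further national patients.

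| Reading | Sum | Primary comparison |
|---|---|---|
| Controls are 15 per centre as written, so the further 75 are program patients | 75 + (75 + 15) + 65 = 230 | 75 control v 90 program |
| The 75 controls come on top of 45 + 45 | 45 + 45 + 75 + 65 = 230 | 120 control v 45 program if all are used |

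Under the first reading, the 90 assessable patients are 6 × 15 program patients and not both arms together. Under the second, each national centre has 120 / 5 = 24 controls, against the stated 15.

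**4. Power of a stepped wedge with these counts.** Figs 1 and 3 are not shown, so the layout is assumed: six periods, one national centre switching at the start of each of periods 2 to 6, and Basse-Normandie's patients spread evenly over all six. The model has fixed period effects and a random cluster effect, with cluster variance 0.05 × 6.25 = 0.3125 and residual variance 0.95 × 6.25 = 5.9375. The SE is the generalised least squares value for the treatment term.

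- *Spread:* each centre's patients are spread evenly over its periods before and after the switch.
- *Concentrated:* each centre's patients fall in the last period before and the first period after the switch.

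| Comparison | Layout | SE | Power, normal test | Power, t on 4 df |
|---|---|---|---|---|
| 75 v 90 | spread | 0.616 | 90% | 68% |
| 75 v 90 | concentrated | 0.445 | 99% | 91% |
| 45 v 45 | spread | 0.812 | 69% | 47% |
| 45 v 45 | concentrated | 0.588 | 93% | 72% |

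The 45 v 45 rows take 9 controls per national centre and 7.5 program patients in each of the six clusters. The difference detectable with 80% power at 75 v 90 (normal test) is 2.80 × 0.445 = 1.25 to 2.80 × 0.616 = 1.73 points.

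**The case against.** The case for the plan is that the mislabelled formula did no harm. If the comparison is 75 v 90, the period-adjusted SE is below the parallel 0.687 in both layouts and normal-test power exceeds 80%, so the parallel formula would have been conservative. This stands, and it limits the point to a justification that is wrong as written.

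Second, the 75 controls are introduced as an addition serving a region-level comparison, and Fig. 3, which is not shown, may display the split. A reader might infer that 230 can only be 75 + 90 + 65. The documents do not support that: 90 program patients are stated nowhere, and 45 + 45 + 75 + 65 gives the same total. The 75 v 90 split is the more plausible because it keeps 15 controls per centre. The other reading does not rescue the text. It contradicts the 15 per centre, the analysis section describes no exclusion of the extra controls, and 45 controls over six clusters remains impossible.

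Third, a reader might infer from the 4-df figures that the trial is underpowered. That is not supported either. Clusters minus two is the convention for a parallel comparison of cluster means. Five clusters here supply within-cluster contrasts, and the article names no degrees-of-freedom method, which may properly sit in an analysis plan. With 20 df the spread 75 v 90 layout gives 87%, not 68%.

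**Conclusion.** Wrong as written, and should be corrected. The 45 per arm and 80% power belong to a parallel 3-versus-3 cluster trial. They contradict the article's own design, in which one cluster is always on the program and five cross over, and its own count of 75 controls. This follows from the text and needs no assumption.

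The size of the effect on power does rest on assumptions: six periods, the two recruitment layouts, ICC 0.05 and SD 2.5. On these, the most plausible comparison of 75 v 90 has normal-test power of about 90% to 99% and a detectable difference of about 1.2 to 1.7 points. A true 45 v 45 wedge would have about 69% to 93%, so the stated 80% could be met only by coincidence of layout. A conservative 4-df reference lowers the 75 v 90 range to about 68% to 91%. Underpowering is not shown.

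**What to change.** - Remove the 45 per arm and the three clusters per arm from the sample size section.
- State how many control and program patients each centre contributes to the primary comparison, and the resulting totals: most plausibly 75 control and 90 program, with Basse-Normandie contributing the 15 patients that the section already specifies and not all 80.
- Restate power and detectable difference from a stepped-wedge calculation with six clusters, period effects, ICC 0.05 and the planned recruitment by centre and period.
- Report power under a small-cluster degrees-of-freedom correction as a sensitivity.

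The cost is one recalculation and some rewording. No extra patients are needed. The restated power may look less favourable once the small number of clusters is allowed for.
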